### Blinding

All study personnel who can be blinded to study aims/hypotheses and group allocation will be blinded. Assessors conducting post-treatment and follow-up assessments will be external to the research team and blinded to study aims/hypotheses and treatment allocation for the full duration of the trial. The assessors will not receive any information about the study design, objectives, or treatment arms to maximize blinding integrity. At each follow-up assessment, participants will be reminded by their assessor not to reveal details about their treatment. Table 3 shows which individuals are blinded to the study aims/hypotheses and/or group allocation.

**Table 3 Tab3:** Individuals involved in the trial who are blinded to study aims/hypothesis and/or group allocation

Individuals involved in the trial	Blinded to study aims/hypotheses	Blinded to group allocation
Principal investigator	No	Yes
Co-investigators	No	Yes
Study coordinator	No	No
Trial therapists	No	No
Study participants	Yes	No
Outcome assessors	Yes	Yes
Data managers	No	Yes
External monitors (Karolinska Trial Alliance)	No	No
Statistician	Yes	Yes
Health economist	No	Yes

The primary analysis will be performed after the trial’s final participant has finished their 1-month follow-up assessment (primary endpoint). When the statistical analyses are completed, and before unblinding, different versions of the abstract will be written, each reaching different conclusions (e.g., intervention A is superior to intervention B, or vice versa). After unblinding, the correct version of the abstract will be used in the final report.

In case of a medical emergency, participants will be encouraged to immediately seek appropriate healthcare and to inform their therapist, who in turn will notify the study coordinator. The local study coordinator will oversee following up the incident. This procedure can be done without unblinding the outcome assessors and, therefore, an emergency unblinding system is not required.

### Patient and public involvement

The feasibility trial preceding the current RCT [29] collected quantitative data on feasibility and preliminary efficacy of the active intervention, as well as detailed qualitative feedback from participating adolescents, their parents, and treating clinicians. Based on this feedback, adjustments to optimize the intervention (e.g., changes to increase participant motivation and improve adherence to the treatment modules) were implemented.

Additionally, the RCT includes a Research Steering Group of young people with BDD and their families. The Research Steering Group provided advice regarding study design, trial conduct, participant engagement, and dissemination activities. This group was recruited from the pool of participants in the feasibility trial and from our specialist clinics. The Research Steering Group also includes representatives from the Swedish service user organizations *Riksföreningen Dysmorfofobi*—*BDD* (the Swedish Body Dysmorphic Disorder Association) and *OCD-förbundet* (the Swedish OCD Association). They have contributed to the optimization of the study design and the optimization of the treatments used in both arms of the RCT. Regular meetings are scheduled to offer updates on the running of the trial and to discuss specific issues related to study implementation and recruitment (e.g., how to increase outreach and detection of BDD cases in youth across the country in order to speed up the recruitment pace). The Research Steering Group members receive compensation for their participation.

### Power analysis

Between-group effect sizes in an RCT comparing face-to-face CBT with an active control in youth with BDD [5] and an RCT comparing ICBT with an active control in adults with BDD [26] were *d* = 1.13 and *d* = 0.94, respectively. Other pediatric ICBT trials similar to ours have reported smaller effect sizes. For example, an ICBT study of adolescent OCD [58] and an ICBT study of adolescent social anxiety disorder [59] reported between-group effect sizes of *d* = 0.69 and *d* = 0.64, respectively. Similarly, an adult BDD trial with an active control condition reported an effect size of *d* = 0.76 [60]. Thus, we have powered our study to be able to detect at least a moderate effect size of *d* = 0.50. A sample size of 128 participants was calculated to be sufficient with a power of 80%, with a 2-tailed *α* = 0.05. An additional 20% of participants will be added to account for potential dropouts. Hence, we aim to recruit a total of 154 participants (77 per group).

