### Randomization and allocation concealment

Participants will be randomized at a 1:1 ratio to one of the two interventions (ICBT or IRT) using randomly varying block sizes. Randomization will be conducted using an online randomization service (ALEA Clinical), set up and monitored by an independent clinical trials unit, the Karolinska Trial Alliance (KTA). The research team will not have access to the random allocation sequence. One or several researchers within the team (according to a task delegation list) will be responsible for the enrollment of participants, randomization, and assigning participants to treatments and therapists. Participants will be informed that they will be allocated to one of two psychological treatments for BDD, without providing specific details about the interventions or the study hypotheses.

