#### Primary outcome analysis

The main analysis will follow a prespecified intention-to-treat statistical analysis plan, which will be finalized and preregistered prior to unblinding. The primary outcome variable is the BDD-YBOCS-A total severity score at the primary endpoint (1-month follow-up). All the randomized participants will be included in a linear mixed-effect model to estimate the difference between group means over time. Linear mixed models use all available data, can properly account for correlation between repeated measurements on the same subject, have greater flexibility to model time effects, and can handle missing data. The model will include fixed effects of time (baseline, post-treatment, and 1-month follow-up), treatment group (ICBT or IRT), site (Region Stockholm, Västra Götalandsregionen, or Region Skåne), and interaction effects of group by time, group by site, site by time, and group by site by time, as well as random intercept to account for individual differences. If the effects of site are not statistically significant, this variable will be dropped from the model to obtain a more parsimonious model. The primary source of inference will be the between-group difference at the primary endpoint (1-month follow-up), estimated from the group by time interaction. Additionally, between-group effect sizes will be estimated using Cohen’s *d*.

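### The dropout allowance is 20% of 128, so 154 keeps the required 128 only if about 17% or fewer 1-month outcomes are missing (minor)

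*Protocol article*

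**What the plan says.** The Power analysis section first fixes the effect: "we have powered our study to be able to detect at least a moderate effect size of *d* = 0.50". It then gives the number needed, "A sample size of 128 participants was calculated to be sufficient with a power of 80" per cent, "with a 2-tailed *α* = 0.05". The allowance follows in one sentence: "An additional 20% of participants will be added to account for potential dropouts". The resulting target is 154, or 77 per group, under the 1:1 allocation described in Randomization and allocation concealment. The Abstract and Trial status repeat the 154.

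The article gives no other dropout figure, and it does not state separately what loss is expected at the 1-month primary endpoint. On the analysis side, Primary outcome analysis says: "All the randomized participants will be included in a linear mixed-effect model to estimate the difference between group means over time". The time points in that model are baseline, post-treatment and 1 month.

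**The concern.** An allowance for dropout is normally sized so that the required number remains after the anticipated loss. Loss is a share of those randomised, so the required number is divided by one minus the loss rate. Here it has been multiplied by one plus 20%, which gives a smaller target.

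Since 20% is the only dropout figure in the article, a reader will naturally take it that the trial can lose 20% of its participants and still have the 80% power quoted just before. On the section's own calculation it cannot. What is at stake is the accuracy of a planning statement that the trial report is likely to repeat. The soundness of the trial is not at stake.

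**Working it through.** **Inputs.** All are from Power analysis unless noted: d = 0.50; two-sided alpha 0.05; power 80%; 128 before allowance; 20% added; target 154 (77 per group); 1:1 allocation (Randomization and allocation concealment).

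**1. Reproduce the 128.** A two-sample t-test (noncentral t) with d = 0.50, alpha 0.05 two-sided and power 0.80 needs 63.77 per arm. Rounded up, that is 64 per arm, 128 in total, with power 80.1%. The normal approximation gives 63 per arm (126), so the article's figure matches the t-test. It contains no adjustment for baseline or repeated measures.

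**2. Reproduce the 154.**
- Multiplying: 128 x (1 + 0.20) = 153.6, rounded up to 154. This is the stated target.
- Dividing: 128 / (1 - 0.20) = 160 (80 per group). This is 6 more than stated.

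Only multiplication gives 154.

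**3. What 154 leaves after 20% loss.** 154 x 0.80 = 123.2, about 61.6 per arm. That is 128 - 123.2 = 4.8 below the required number.

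**4. The loss that 154 can absorb.** 1 - 128/154 = 26/154 = 16.9%.

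**5. Size of the shortfall, by the same t-test at d = 0.50.**

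| Target | Loss | Remaining per arm | Power |
|---|---|---|---|
| 154 | 16.9% | 64 | 80.1% |
| 154 | 20% | 61.6 | 78.6% |
| 160 | 20% | 64 | 80.1% |

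The difference is 80.1 - 78.6 = 1.5 percentage points. With 61.6 per arm, the effect detectable at 80% power is d = 0.509.

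**6. Can the planned model be assumed to make up the difference?** The article gives no correlation between baseline and 1-month scores, so the values below are assumptions. They take 61.6 per arm, equal variances, and d on the raw-score standard deviation. Two simple readings of the model are compared:
- a between-group contrast in change from baseline, where the effective d is 0.50 / sqrt(2(1 - r));
- an analysis adjusted for baseline as a covariate, where the effective d is 0.50 / sqrt(1 - r^2).

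| Assumed r | Change contrast | Baseline as covariate |
|---|---|---|
| 0.3 | 64.3% | 82.3% |
| 0.5 | 78.6% | 88.9% |
| 0.6 | 86.8% | 93.1% |

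Power could therefore lie below or above 78.6%, depending on the correlation and on how the model is set up. Primary outcome analysis enters baseline as one of the outcome time points, not as a covariate, and takes the 1-month difference from the group-by-time interaction. The article does not settle where in this range the planned analysis falls.

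**The case against.** **No printed number is wrong.** The sentence promises 20% on top of 128, and 154 is that. The section never says that 20% are expected to drop out, nor that 80% power holds after a 20% loss. This stands. The stronger reading, that the article asserts 80% power at 20% dropout and is therefore false, is something a reader might infer but the text does not say. What remains is that the addition is explicitly there to cover dropouts, and that it covers 16.9%, a figure that appears nowhere.

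**The effect is trivial.** This also stands. The shortfall is 1.5 points of power, and the planning effect of 0.50 lies below every between-group effect cited in Power analysis (0.64 to 1.13). At d = 0.64 the same t-test gives 94.1% power with 61.6 per arm and 94.9% with 64. A reader might infer that the trial is underpowered; the figures do not support that.

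**The 123 belongs to a comparison of participants with 1-month data, which is not the planned analysis.** This is correct. The mixed model uses all available data, and under Treatment format and therapist support those who do not finish treatment are still invited to follow-up, so stopping treatment need not mean a missing outcome. But a participant with no 1-month score contributes only partial information about the 1-month difference. This limits what 78.6% can be taken to mean; it does not make 154 an allowance for 20% loss.

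**Baseline data recover the shortfall.** This is tempting, but the article does not support it. Power analysis assumes no correlation, and on one plausible reading of the model a low correlation reduces power.

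**Conclusion.** Wrong as written, and minor. The target of 154 is 128 increased by a fifth. If the 20% is meant as the share of randomised participants without a 1-month outcome, about 123 remain where 128 are required. Retaining 128 would take 160, and 154 is enough only up to a loss of about 17%.

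On the calculation behind the 128, the cost is 1.5 points of power (78.6% against 80.1%) or a detectable d of about 0.51. The conclusion rests on two assumptions: that the 20% describes anticipated loss at the primary endpoint, which is the natural reading but is not stated, and that the unadjusted two-sample t-test is the yardstick, since it reproduces the article's figure. The 78.6% should not be read as the power of the planned mixed model. Nothing here calls the design or the recruitment target into question.

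**What to change.** Keep 154 and restate the allowance in Power analysis, for example: *The target of 154 retains the 128 required for 80% power at d = 0.50 if up to about 17% of 1-month outcomes are missing; at 20% missing, power by the same two-sample calculation is about 78.6%.*

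Do not add that baseline adjustment recovers the shortfall unless the sponsor also states the model and the assumed correlation on which that rests.

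The cost is one sentence and a slightly less favourable planning figure. No extra participants are needed. Trial status reports 100 of 154 recruited as of 21 August 2026 and foresees further protocol versions, so the wording can go into the next one.

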### Statistical analysis

Statistical analyses relating to the clinical efficacy and 6-month durability aims will be conducted in-house by the study coordinator at the Stockholm site (author [name]) and then independently replicated by personnel at the Biostatistics Core Facility at Karolinska Institutet (under the direction of author [name]). The economic evaluation will be conducted under the supervision of author [name] at Karolinska Institutet, who will also be blinded to group allocation. A full statistical and health economic analysis plan (see Supplementary File 2) will guide the statistical and health economic analyses. This plan will be finalized before the last participant has reached the primary endpoint. In the possible case that any information regarding statistical analyses would differ from this protocol, the latest version of the statistical and health economic analysis plan will be considered the original source to guide analytical decisions.

The demographic information collected at baseline will be summarized and presented in a table, by randomization arm. Categorical variables will be reported as counts and percentages. Continuous variables will be summarized as means, medians, and interquartile ranges, as appropriate. According to CONSORT recommendations, no statistical tests will be performed to assess baseline differences between study arms [31]. No interim analysis is planned.

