### Safety procedures

A questionnaire will be administered to systematically assess adverse events throughout the trial. The questionnaire was developed by the research team and includes a checklist of expected adverse events based on previous trials as well as a free text box where other, not listed adverse events can be registered. Additionally, high scores on the SMFQ (depressive symptoms), with the additional suicide item, and the DSHI-Y-7 (self-harm) might also be indicators of adverse events. Scores ≥13 points on the SMFQ-C or SMFQ-P, or scores of 2 (“*I have had thoughts about death and of taking my life, but would never do it*”) or 3 (“*I have had thoughts about death and of taking my life*”) points on the suicide item on the SMFQ-C, will automatically raise a flag in the BASS system that will directly notify members of the research team to follow this up (via telephone) with the participant and their parents/caregivers. This will be recorded as an adverse event if the score is greater than their baseline score. The research team can also be notified about adverse events through direct (text or telephone) communication with the participant.

All adverse events will be documented at each of the sites by the corresponding local study coordinator in a specific log (including date, recorded clinical symptoms, and a brief description of the event), which in turn will be shared with the external monitor, the KTA. All adverse events will be summarized by number (frequencies and percentages), nature, severity, and whether they are expected or unexpected. The event will be classified as expected if it was listed as such in the study protocol (e.g., increased severity of BDD symptoms, lower mood, increased risk of self-harm, suicidal ideation, and/or suicide attempt; see Supplementary File 1 for the full list). If the event is not listed, then it will be classified as unexpected. If there are any serious adverse events (i.e., those resulting in death, life-threatening, requiring hospitalization, resulting in disability or incapacity, or considered medically significant by the principal investigator), the study coordinator and the principal investigator will judge whether these are related to the treatments provided. Events will be considered as potentially treatment-related up to the 6-month follow-up.

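### The first run of the primary analysis is assigned to the study coordinator, whom Table 3 lists as unblinded, so the before-unblinding safeguards do not bind the lead analyst

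*Protocol article*

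**What the plan says.** Under Statistical analysis, the protocol article states that the efficacy analyses "will be conducted in-house by the study coordinator at the Stockholm site". The same sentence adds that staff of the Biostatistics Core Facility will then replicate them independently.

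The Blinding section explains that "Table 3 shows which individuals are blinded to the study aims/hypotheses and/or group allocation". Two rows of that table matter here. With the columns in the order hypotheses, then allocation, they read "Study coordinator No No" and "Statistician Yes Yes". The principal investigator and co-investigators are listed as aware of the hypotheses but blinded to allocation.

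Two safeguards are tied to the moment of unblinding:

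- Blinding section: "When the statistical analyses are completed, and before unblinding, different versions of the abstract will be written". The matching version is used once the arms are revealed.
- Primary outcome analysis section, on the analysis plan: "which will be finalized and preregistered prior to unblinding".

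The Primary outcome analysis section also contains a data-dependent step. The mixed model includes site and its interactions with group and time, and site is removed if its effects are not statistically significant.

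**The concern.** Both safeguards assume that whoever produces the primary result does not yet know which arm is which. The article gives the first run to a role that its own table marks as knowing both the allocations and the hypotheses.

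At stake are the modelling decisions behind the primary comparison, the between-group difference in BDD-YBOCS-A at the 1-month follow-up. Where the rules leave room for interpretation, a lead analyst who knows the arms and the expected direction can see which reading favours which treatment. A reader who learns that analysis and abstract drafting preceded unblinding would also take this to cover the analyst, which Table 3 contradicts.

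**Working it through.** No figure in the plan bears on this point, so the check is a comparison of sections.

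1. **Who analyses first.** Statistical analysis section: the study coordinator at the Stockholm site. The Core Facility follows; the sentence fixes that order.

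2. **What that person knows.** Table 3: the study coordinator is blinded to neither hypotheses nor allocation. The table has one row for the role and makes no exception for Stockholm. Nothing elsewhere in the article describes masking the coordinator for the analysis.

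3. **What the safeguards assume.** The Blinding section orders the events as analyses completed, alternative abstracts written, arms revealed. The Primary outcome analysis section dates the final plan by reference to unblinding. For someone who already knows the allocations, the last event in that sequence has happened before the first.

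4. **Whether coded labels would help.** They would not for this analyst. A person who knows individual allocations can identify arm A from a few records. The data also reveal the arm directly: under Secondary outcome measures, adherence is recorded on the PEAS or the PRAS depending on the assigned treatment.

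5. **Whether replication restores the safeguard.** Only in part. If the Core Facility is the statistician of Table 3, which the article does not say, the second run is blinded. It can confirm that the specified model was fitted correctly. Coming second, it cannot make blind the choices already taken in the first run.

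6. **Whether there are choices to take.** At least one is visible. The model has four terms involving site: the main effect, group by site, site by time, and group by site by time. The article does not say whether they are tested jointly or singly, at what level, or whether all go together. This step affects how the group-by-time contrast is estimated.

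7. **Whether an alternative exists.** It does. The article's general statement is that everyone who can be blinded will be, and it already involves a separate analysis group.

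The Statistical analysis and Blinding sections therefore disagree on whether the primary analyst is blinded, and the article does not resolve it.

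**The case against.** The strongest reply is that the plan contains more protection than the first half of the sentence suggests. Independent replication is promised in that same sentence. The principal investigator and co-investigators are listed as blinded to allocation, so drafting alternative abstracts still constrains them. Outcome assessors are external and blinded, the primary outcome has full source data verification at baseline and the primary endpoint, and the analysis follows a prespecified plan. The site step is a significance rule, and it would depend on the data for a blinded analyst too. The full analysis plan is not shown and may describe masking.

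Most of this stands and limits the point. It does not remove it: none of these measures blinds the person who runs the primary analysis first, and the inconsistency lies within the article itself.

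Several stronger readings are tempting but not supported:

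- **That no blinded analysis is planned at all.** The replication may well be blinded, and the abstract step keeps some force for the investigators.
- **That durability results are equally exposed.** The 3- and 6-month follow-ups are described as uncontrolled, and the long-term model has no group term, so knowledge of allocation matters much less there.
- **That keeping or dropping site shifts power by a known amount.** The article gives neither the site shares nor the exact contrast, so any figure would rest on assumptions.
- **That the principal investigator's blinding is contradicted because "the study coordinator and the principal investigator will judge whether these are related to the treatments provided".** Relatedness can be judged without knowing the arm, and the text does not say that allocation is disclosed.
- **That the analysis plan is locked too late.** "This plan will be finalized before the last participant has reached the primary endpoint" is ordinary practice, as is giving the plan precedence over the protocol.

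**Conclusion.** The point holds in a limited form. The role assigned the first run of the primary efficacy analysis is listed as unblinded to hypotheses and allocation. For that analyst, the safeguards tied to unblinding have no force. Across the trial they are weakened, not absent.

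The size cannot be expressed as a number. The exposure is confined to modelling choices for the between-group comparisons, chiefly the handling of site, under a prespecified plan and with a later independent check. There is no evidence that any choice has been or would be made improperly.

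The conclusion assumes that the Table 3 row for the study coordinator applies to the Stockholm coordinator, as nothing in the article says otherwise. The statement that a blinded replication exists assumes that the Core Facility is the statistician of Table 3. If the unseen analysis plan masks the lead analyst in some effective way, the article's wording would still need to be aligned with it.

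**What to change.** Swap the order of the two roles already planned. The Biostatistics Core Facility, confirmed as the blinded statistician of Table 3, runs and locks the primary analysis on arms coded A and B. Fields that reveal allocation, such as PEAS and PRAS, are withheld from that export. The coordinator's run then becomes the replication.

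If the order cannot change, say in the Statistical analysis and Blinding sections that the primary analyst is unblinded and only the replication is blinded, and carry that statement into the trial report.

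The swap needs no new staff, since both groups already analyse the data. It costs a wording change, preparation of a masked export, and somewhat more Core Facility time up front. The article says that analysis for the primary aim starts only after the last participant reaches the primary endpoint, so the change can still be made before any result exists.
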